## Abstract

**Background:**

Although the negative impact of sleep apnea on the clinical course of acute ischemic stroke (AIS) is well known, data regarding non-invasive ventilation in acute patients are scarce. Several studies have shown its tolerability and safety, yet no controlled randomized sequential phase studies exist that aim to establish the efficacy of early non-invasive ventilation in AIS patients.

**Methods/design:**

We decided to examine our hypothesis that early non-invasive ventilation with auto-titrating bilevel positive airway pressure (auto-BPAP) positively affects short-term clinical outcomes in AIS patients. We perform a multicenter, prospective, randomized, controlled, third rater- blinded, parallel-group trial. Patients with AIS with proximal arterial obstruction and clinically suspected sleep apnea will be randomized to standard stroke care alone or standard stroke care plus auto-BPAP. Auto-BPAP will be initiated within 24 hours of stroke onset and performed for a maximum of 48 hours during diurnal and nocturnal sleep. Patients will undergo unattended cardiorespiratory polygraphy between days three and five to assess sleep apnea. Our primary endpoint will be any early neurological improvement on the NIHSS at 72 hours from randomization. Safety, tolerability, short-term and three-months functional outcomes will be assessed as secondary endpoints by un-blinded and blinded observers respectively.

**Discussion:**

We expect that this study will advance our understanding of how early treatment with non-invasive ventilation can counterbalance, or possibly reverse, the deleterious effects of sleep apnea in the acute phase of ischemic stroke. The study will provide preliminary data to power a subsequent phase III study.

**Trial registration:**

Clinicaltrials.gov Identifier: NCT01812993

## Background

Stroke still constitutes a leading cause of death and ranks number one among all causes of serious long-term adult disability in Europe and the United States [1,2], underscoring the need for adjuvant acute and preventive stroke therapies that reduce both the devastating human and economic burden of this disease.

More than two-thirds of acute ischemic stroke (AIS) patients suffer from sleep apnea of variable degree compared to 5 to 15% in the general population [3-6]. Moreover, in a prospective cohort study, patients with moderate to severe obstructive sleep apnea (OSA) had an almost two-fold increased risk for stroke and death after adjustment for other traditional vascular risk factors, thus establishing OSA as an independent risk factor [7,8]. Following stroke, sleep apnea negatively affects the length of hospitalization and short-term as well as long-term outcomes, likely through its association with an increased risk of neurological deterioration during acute and subacute phases of stroke [4,9-12]. Neurological deterioration during the early phase of AIS can occur between one and two out of five patients and it is independently predicted by sleep apnea and associated with unfavorable outcome [9,13].

Numerous studies including serial transcranial Doppler (TCD) in patients with AIS provided evidence that persisting large-artery steno-occlusive disease and corresponding collateral failure, leading to depletion of oxygen and nutrients to penumbral tissues, appear to be the most relevant pathogenic mechanisms for neurological deterioration [14-17]. Thus, it seems intuitive that further hemodynamic and perfusion derangements may do harm by facilitating hypoperfusion and ultimately lead to expansion of infarction to penumbral areas (or even oligemic tissues surrounding the ischemic penumbra) with neurological deterioration as the clinical correlate [18].

Several pathophysiological conditions associated with sleep apnea are believed to account for acute harmful effects on ischemic brain [19]. Recurrent nocturnal apneic episodes promptly entail intermittent hypoxemia, intrathoracic pressure changes and activation of the sympathetic nervous system resulting in cardiac arrhythmias and marked blood pressure swings [20,21]. The cerebral autoregulatory system is essential to compensate for changes in systemic hemodynamics and to avoid harmful hypo- or hyperperfusion of brain tissue. The fate of ischemic brain tissues particularly in the setting of large steno-occlusive disease already depend on dilated arteries with no further or only minimal residual vasomotor capacity [22-24] to counteract apnea-associated blood pressure changes and maintain blood flow according to local metabolic needs [19]. In fact, patients with sleep apnea generally have impaired cerebral vasoreactivity, even during wakefulness, potentially explaining their particular vulnerability to stroke-associated hemodynamic derangements [25-28]. Repetitive oxygen desaturations in cerebral ischemic tissue during apneic periods may further compromise functional and structural integrity of neuronal cells [29]. Additionally, hypercapnia may lead to depletion of the collateral blood flow when vessels in the non-ischemic area dilate more leading to blood flow diversion from the ischemic area to the non-ischemic areas, possibly further worsening hypoperfusion in the ischemic brain area [23,30,31]. This ‘cerebral blood flow steal’ phenomenon was demonstrated by TCD in real time in AIS patients during voluntary breath holding and led to early neurological deterioration in those with acute proximal arterial obstructions and excessive daytime sleepiness [10]. When found during the initial hospitalization for AIS, this so called ‘reversed Robin Hood syndrome’ led to a four-fold increase in stroke recurrence within the same arterial territory [11].

Maintenance of stable systemic and cerebral hemodynamics, as well as adequate and constant brain tissue oxygenation, plays a crucial role in the management of AIS [32]. The ischemic penumbra may be present for many hours and be amenable to reperfusion. Consequently, any treatment that potentially maintains or augments cerebral perfusion may be justified [33]. Non-invasive ventilation with either continuous (CPAP) or bilevel positive airway pressure (BPAP) is the treatment of choice for sleep apnea. Although some studies have shown the safety and beneficial effects of CPAP and BPAP by improvement of quality of life and reduction of cardio- and cerebrovascular morbidity and mortality in the general sleep apnea population [34,35], their role in AIS patients remains to be elucidated. Most previous investigations were conducted beyond the (hyper-) acute phase of ischemic stroke and pursued secondary stroke prevention goals rather than acute effects. For example, two studies confirmed safety and tolerability, and pointed to a potential short-term treatment effect of prompt initiation of non-invasive ventilation in the acute phase of stroke when hemodynamically compromised tissue can potentially be salvaged [36,37]. In the first study, an observational study, AIS patients with proximal persisting arterial occlusions and suspected or known OSA had a tendency towards early neurological improvement (median National Institutes of Health Stroke Scale (NIHSS) score decrease by 2 points) during the hospital course when BPAP was initiated within the first 24 hours of admission, as compared with those who did not receive BPAP (median NIHSS score decrease by 1 point, *P* = 0.078) [36]. The other study randomly assigned fifty patients in the first night after AIS to either CPAP for three nights or control [37]. The investigators found that CPAP treatment was feasible, safe and associated with a greater neurological improvement until day eight in patients who tolerated CPAP well when compared with control patients (NIHSS 2.3 versus 1.4, *P* = 0.022).

As data on the use of non-invasive ventilation in the acute phase of ischemic stroke are lacking and its potential benefit on stroke outcomes is controversial [38], a randomized controlled efficacy trial appears justified as being timely and needed. The choice of using an auto-titrating BPAP ventilation mode is based on the fact that AIS patients will not have the necessary time or access to facilities to undergo comprehensive sleep laboratory testing prior to start of treatment. Auto-BPAP adapts pressure settings automatically according to apnea frequency recorded in real-time from breath-to-breath, thus sparing manual titration of therapeutic pressures. Also, BPAP mode delivers pressure levels for inspiration and expiration separately, easing inspiration while ensuring alveolar ventilation and splinting the airway, which has several advantages over standard CPAP that applies a fixed pressure setting during the entire respiratory cycle [39]. Collectively, auto-BPAP may be superior particularly in patients who require higher pressure levels [39,40] and produces improved patient adherence, a well-known issue in recent studies that may be even more important for stroke patients who may not have appropriate understanding and motivation to allow themselves to be exposed to mask and airflow pressures. Finally, this approach could be utilized in stroke centers without experience in sleep medicine.

## Methods

### Study design

This is an international, multicenter, prospective, randomized, controlled, third rater-blinded, parallel-group phase II study (Clinicaltrials.gov identifier: NCT01812993). A double-blind study design would require sham ventilatory treatment that is impossible in this setting. A sham mask device with subtherapeutic pressures may also pose a risk of harm as it will likely preclude adequate ventilation and increase the respiratory ‘dead space’ volume. Thus, to minimize bias associated with an open-label study, a trained neurologist or nurse blinded to treatment allocation will assess the primary and, whenever applicable, secondary efficacy outcomes. The study protocol has received full ethics approval by the Institutional Review Board of the University of Technology Dresden (Reference number: EK 362112012).

### Patient population

Using a convenience sampling method, patients presenting to one of the participating stroke centers with AIS due to intra- or extracranial arterial steno-occlusive obstruction and clinically suspected sleep apnea will be eligible for the study. Patients will have to meet the following inclusion and exclusion criteria:

#### Inclusion criteria

•Male and female patients 18 to 80 years;

•Clinical suspicion of an AIS (measurable or fluctuating neurological deficit with a NIHSS ≥ 4 points) within 24 hours from symptom onset;

•Extracranial (that is, internal carotid artery) or intracranial (that is, internal carotid artery; middle/anterior/posterior cerebral arteries) ≥ 50% stenosis, near-occlusion or occlusion diagnosed by ultrasound, computed tomography angiography (CTA) or magnetic resonance angiography (MRA), corresponding to the acute neurological deficit;

•High risk of having sleep apnea (classified by the Berlin sleep apnea questionnaire); or history of known sleep apnea; or witnessed repetitive apneic episodes during sleep or somnolence during hospitalization;

•Written informed consent by participants; alternatively by proxy or two physicians when not obtainable by patient or proxy (according to local regulations).

#### Exclusion criteria

•Perceived course towards malignant middle cerebral artery infarction;

•Vertebrobasilar ischemic stroke;

•Immediate or perceived need for intubation;

•Known sleep apnea currently on non-invasive ventilatory treatment;

•Standard contraindications for non-invasive ventilatory treatment;

•Pre-morbid modified Rankin scale (mRS) score ≥ 3;

•Severe comorbidities (that is, severe heart failure, severe obstructive lung disease, active malignant disease, severe dementia);

•Pregnant and breast-feeding women;

•Participation in another clinical trial other than standard-of-care registry.

### Randomization

All randomization procedures are prepared and monitored by the Dresden Coordination Center for Clinical Studies, independent of patient recruitment and implementation of the assignment. After eligibility for the study has been confirmed, written informed consent obtained and baseline assessments completed, a 1:1 randomized allocation to either standard stroke care alone (no ventilatory treatment = control) or standard stroke care plus non-invasive ventilatory treatment with auto-BPAP will be performed according to a computer-generated random number (nQuery Advisor® PPS 6.01, Saugus, MA, USA) that is provided via the online Research Electronic Data Capture (REDCap) system [41]. The allocation sequences are concealed from investigators involved in patient recruitment and collection of outcome data. Stratified block randomization with strata for study site and stroke severity as defined by the NIHSS (that is, 4 to 10 and > 10 points) will be used, wherein the block size is fixed and will not be communicated to any of the investigators with clinical involvement in this trial.

### Study procedures

Study physicians will obtain baseline NIHSS scores, determine patient eligibility and obtain informed written consent from each patient prior to any study-related procedures. Patients allocated to the active group will receive non-invasive ventilatory treatment with auto-BPAP (Philips Respironics, Auto-BIPAP Biflex®, Herrsching, Germany) within 24 hours of symptom onset, and for a maximum of 48 hours during diurnal and nocturnal sleep or somnolence, from the beginning of study randomization (Figure 1). This approach warrants that all patients in the active group will receive an intention-to-treat all potential apneic episodes independently of their sleep cycle and somnolence. During the study period, oral and tube feeding intake will be allowed according to local institutional protocols. The auto-BPAP device automatically adjusts expiratory (EPAP) and inspiratory positive airway pressure (IPAP) levels to meet patients’ needs and will be configured to pressure settings that are identical in all patients in the active group: possible minimum EPAP 4 mbar; possible maximum IPAP 25 mbar; maximum difference between EPAP and IPAP (delta) 8 mbar; Biflex 2. The device records sleep-related respiratory events as well as duration of its use. Attachment of the device and initiation of treatment is performed by the study personnel who will receive training specific to the device by a sleep neurologist experienced with the study device.

**Figure 1 F1:**
[figure not shown]
**Study flowchart.** NIHSS indicates National Institutes of Health Stroke Scale Score. BPAP, bilevel positive airway pressure. mRS, modified Rankin Scale.

All patients will undergo a diagnostic unattended cardiorespiratory polygraphy between days three and five from enrollment for assessment of sleep apnea using a previously established protocol [5]. A rater experienced in sleep medicine and who is unaware of group allocation and clinical data will analyze the sleep polygram.

### Primary aim

The primary aim is to determine if early auto-BPAP initiated within the acute phase of ischemic stroke affects short-term clinical outcome. The signal-of-efficacy in these patients will be determined if these early changes in the neurological deficit could be sustained at three months from symptom onset.

### Primary endpoint

Early neurological recovery will be assessed as any improvement on the NIHSS score at 72 ± 12 hours from randomization. Physicians or qualified study personnel, other than those involved in acute treatment (that is, blinded to randomization) and who are certified in performing NIHSS scoring, will obtain the NIHSS scores.

### Secondary aims

Secondary aims are comprised of the assessment of tolerability and safety of auto-BPAP initiated within the acute phase of ischemic stroke, as well as its possible effect on other clinical outcomes during hospitalization and follow-up (signal-of-efficacy).

### Secondary endpoints

Tolerability will be assessed by patient adherence to auto-BPAP (defined as tolerating the treatment during sleep or somnolence for at least four hours continuously).

*Safety* will be assessed by:

(i) frequency of serious adverse events (that is, aspiration, aspiration pneumonia defined as combined radiologic, white blood count and clinical findings, respiratory failure with/without intubation) during treatment period that in the opinion of the study physician are causatively and timely (for a maximum of 72 hours from treatment initiation) related to auto-BPAP. For comparison, patients in the control group will be monitored for respiratory complications within 72 hours from randomization. All deaths in both groups during hospital stay;

(ii) frequency of all complaints and possible side effects of auto-BPAP (that is, local irritation of skin/mucosa, mucosal dryness, nausea/vomiting);

(iii) any concerns by hospital nursing staff will be documented as adverse events since patients will be under standard of care repeated assessments set by admission protocols and treating physicians.

Signal-of-efficacy:

Clinical and functional outcomes will be assessed by:

(i) frequency of neurological deterioration (increase in baseline NIHSS score ≥ 4 points) at 24, 48 and after 72 hours from randomization by blinded observers;

(ii) frequency of early neurological improvement (decrease in baseline NIHSS score ≥ 4 points) at 24, 48 and after 72 hours from randomization by blinded observers;

(iii) good functional outcome (mRS score 0 to 2) at discharge and at three months by blinded observers, and ordinal analysis of the mRS at three months;

(iv) all deaths and any TIA or new ischemic stroke during hospitalization or within three months of protocol initiation.

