### Data Safety Monitoring Board (DSMB)

Serious adverse events (SAE) as described above and unexpected SAE will be collected for the first 72 hours from initiation of auto-BPAP. All SAEs will be reported by fax or Email within 24 hours from occurrence to the DSMB that is composed of two clinicians and a biostatistician at the University of Technology Dresden who is not involved in the execution of this study. In the event of an SAE, subjects in the auto-BPAP arm will immediately have the procedure terminated, and will receive stabilizing procedures. All SAEs must be reported within 24 hours, and will require submission of incident findings and associated events by the local principal investigator to the DSMB for adjudication. From our pilot study [36], we expect SAEs to occur in less than one in ten enrolled patients. If there is one SAE in the first 10 patients, the study will continue. If there are two SAEs in the first 10 patients then the study will stopped and DSMB will make recommendations if certain criteria/exposures need to be modified. The study will be halted if treatment with auto-BPAP results in more than two SAEs per 10 patients. Thereafter, DSMB will receive monthly enrollment/safety/outcomes reports. Additionally, DSMB will be convened any time that safety or data concerns arise. DSMB will also have access to unblinded data, to make decisions if higher than expected rates of SAEs are being outweighed by potential benefits; no further criteria for stopping the trial will be set as limited data are available to guide such algorithms at this point.

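### In the respiratory part of safety item (i), auto-BPAP events count only if serious and judged device-related, while control events carry neither condition, so that comparison is biased toward auto-BPAP looking safe

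*Protocol article*

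**What the plan says.** **Secondary endpoints, safety item (i).** The measure opens as "frequency of serious adverse events (that is, aspiration, aspiration pneumonia defined as combined radiologic, white blood count and clinical findings" and goes on to respiratory failure. It is confined to the treatment period and to events "that in the opinion of the study physician are causatively and timely (for a maximum of 72 hours from treatment initiation) related to auto-BPAP". The next sentence sets up the comparator: "For comparison, patients in the control group will be monitored for respiratory complications within 72 hours from randomization". The item closes by counting in-hospital deaths in both arms.

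**Who judges.** The abstract states: "Safety, tolerability, short-term and three-months functional outcomes will be assessed as secondary endpoints by un-blinded and blinded observers respectively". The Study design section promises blinding for efficacy only: "a trained neurologist or nurse blinded to treatment allocation will assess the primary and, whenever applicable, secondary efficacy outcomes".

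**Treatment timing.** Under Study procedures, auto-BPAP is given "for a maximum of 48 hours during diurnal and nocturnal sleep or somnolence", counted from randomization.

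**SAE collection.** The Data Safety Monitoring Board section says: "Serious adverse events (SAE) as described above and unexpected SAE will be collected for the first 72 hours from initiation of auto-BPAP".

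**The concern.** The control sentence shows that the two counts are meant to be set side by side, and the Planned statistical analysis section provides chi-square or Fisher tests for categorical secondary endpoints. The two numerators are not the same quantity. An aspiration pneumonia in an auto-BPAP patient disappears from the count if the physician puts it down to the stroke. The same pneumonia in a control is counted, because a device-relatedness condition cannot apply there and no other condition is stated. The relatedness call is made with knowledge of allocation.

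At stake is the respiratory safety signal for mask ventilation in acute stroke. The article names safety among the secondary aims and says the trial will supply preliminary data for a phase III study. A real excess of respiratory events could look neutral, and no difference could look like protection.

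**Working it through.** **1. The two definitions side by side (safety item (i))**

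| | Auto-BPAP arm | Control arm |
|---|---|---|
| Events | aspiration, aspiration pneumonia, respiratory failure | respiratory complications |
| Seriousness | serious only | not stated |
| Relatedness | judged due to auto-BPAP by the study physician | none possible |
| Clock starts | treatment initiation | randomization |

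The seriousness and relatedness conditions act on one arm only, and each can only lower that arm's count.

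**2. Size of the relatedness filter.** The document gives no safety comparison, margin or power, so there is no stated figure to reproduce. Inputs:

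- Patients per arm: 30 (Sample size section).
- Expected SAE frequency: below one in ten enrolled patients (DSMB section). This is the only rate given.
- True respiratory-event risk p, the same in both arms: assumed 5% to 20%. Values above 10% exceed the document's expectation and only show the range.
- Share a of auto-BPAP-arm events judged related: not given; assumed 25% to 75%.

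Formulas: counted risk in the auto-BPAP arm = p × a; counted risk in controls = p; apparent risk ratio = a; apparent risk difference = p × a − p.

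| p | a | Auto-BPAP counted | Control counted | Difference (points) | Expected events per 30 |
|---|---|---|---|---|---|
| 5% | 25% | 1.25% | 5% | −3.75 | 0.375 vs 1.5 |
| 5% | 75% | 3.75% | 5% | −1.25 | 1.125 vs 1.5 |
| 10% | 25% | 2.5% | 10% | −7.5 | 0.75 vs 3.0 |
| 10% | 50% | 5% | 10% | −5.0 | 1.5 vs 3.0 |
| 10% | 75% | 7.5% | 10% | −2.5 | 2.25 vs 3.0 |
| 20% | 25% | 5% | 20% | −15 | 1.5 vs 6.0 |
| 20% | 75% | 15% | 20% | −5 | 4.5 vs 6.0 |

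At a = 100% the difference is 0. Below that it always favors auto-BPAP.

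**3. What could be masked.** If the true risk ratio is R, the plan shows R × a. It shows 1.0 when R = 1/a, that is 1/0.25 = 4.0, 1/0.50 = 2.0 or 1/0.75 = 1.33.

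**4. Clock.** Treatment is timed from randomization, so initiation should follow soon after and the two 72 h windows should nearly coincide. Two loose ends remain. A patient allocated to auto-BPAP who never starts has no window under the wording of item (i), although the primary intention-to-treat analysis retains that patient. Item (i) also confines events to the treatment period, at most 48 h under Study procedures, yet allows up to 72 h in the same sentence.

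**The case against.** **Other safety measures are symmetric.** In-hospital deaths are counted in both arms. Nursing concerns in item (iii) are not restricted by arm. Neurological deterioration is rated by blinded observers, and deaths, TIA and new stroke are followed to three months. This stands. A reader might infer that the whole safety assessment is biased; the document does not support that. A respiratory harm that led to death or marked deterioration would still show. A non-fatal pneumonia judged unrelated might not.

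**DSMB oversight.** The DSMB section also covers unexpected SAEs, asks for SAE reports within 24 hours, sends them for adjudication and gives the board unblinded data. It specifies terminating the procedure for the auto-BPAP arm only, which suggests reporting is not confined to that arm. A reader might infer that control-arm SAEs go uncollected; the text does not show this. A reader might also infer that the early SAE rule is weakened, but the document does not say whether the relatedness filter feeds that rule, or whether its ten patients are enrolled or auto-BPAP patients. Oversight helps only in part: the section adopts the SAE definition given earlier, adjudication does not redefine the endpoint, and the collection start has no meaning for controls.

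**Wording.** The control sentence does not say that every respiratory complication is counted. That is the natural reading, since no filter is stated, but it is a reading. The sentence on physician opinion does not mention blinding; that rests on the abstract and on the open-label design.

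**Size and priority.** The attribution share is unknown. At 10% risk and half attributed, the distortion is 3.0 − 1.5 = 1.5 expected events in 30 patients. Safety is a secondary aim, and the confirmatory NIHSS analysis is untouched. Both statements are correct and limit the weight of the point, but neither makes the two counts comparable.

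**Conclusion.** The point holds for the respiratory events in safety item (i) and no further. The two arms are counted under different definitions, and the extra conditions can only remove events from the auto-BPAP arm. The direction of that effect follows from the wording; it is nil only if every auto-BPAP-arm event is serious and judged related. This is a statement about the filter, not about every possible source of ascertainment bias.

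The size rests on assumption. With equal true risk of 10% and 25% to 75% of events attributed, the plan would show 2.5% to 7.5% against 10%, a spurious difference of 2.5 to 7.5 points in favor of auto-BPAP. Larger differences need risks above the document's own expectation. The difference in clocks is minor. In-hospital deaths and the NIHSS endpoints are not affected.

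**What to change.** In Secondary endpoints, safety item (i):

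- For the between-arm comparison, count aspiration, aspiration pneumonia and respiratory failure (with or without intubation) in both arms, under one seriousness criterion, within 72 h of randomization and regardless of judged cause.
- Report the physician's relatedness judgment separately, as a descriptive item in the auto-BPAP arm.
- Keep deaths on their existing in-hospital window. Moving them into the 72 h list would narrow a measure that is already symmetric.
- Remove the conflict between the treatment period and the 72 h limit by using the single window above.

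In the Data Safety Monitoring Board section, state the SAE collection window from randomization for both arms, since initiation of auto-BPAP does not exist for controls or for allocated patients who never start.

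Cost: mainly wording, plus some extra recording. The reported event count in the auto-BPAP arm will be higher. Recruitment began in May 2013 and is ongoing, and the document does not say whether unattributed respiratory events in the auto-BPAP arm are being recorded. If they are not, they would have to be recovered for patients already enrolled, so the change is best made early.
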